### Staff evaluation

Staff across the secure services will be asked to complete questionnaires to assess their attitudes and beliefs about physical health, and the ward atmosphere (ESSEN-Climate Evaluation Schema (ESSEN-CES; [44]), Metabolic-Barriers, Attitudes, Confidence and Knowledge Questionnaire (M-Back Questionnaire; [45]). Staff on non-participating wards will also be encouraged to complete questionnaires to allow comparison of the overall ward environment when not taking part in a physical health trial. Clinical staff will be encouraged to provide feedback in a specially designed questionnaire, or interviews after Motiv8 has taken place.

### Fidelity and facilitator evaluation

Fidelity assessments will be undertaken to see whether the intervention can be delivered according to protocol and inform a definitive trial. Adherence checklists specific to each component will be completed at the end of each session by facilitators. Assessment of facilitator performance will be conducted throughout the trial, during regular monitoring and supervision. Feedback will be collected from facilitators at the end of the trial and feedback strategy sessions will be held with facilitators and the research team. Intervention fidelity assessments, feedback and outcome measures will be used to inform a definitive trial.

### Analysis

A detailed Statistical Analysis Plan will be drafted by the study statistician prior to data analysis and a Health Economics Analysis Plan will be drafted by the study health economist. Quantitative analysis will be conducted according to intention-to-treat and reported according to CONSORT guidelines for cluster randomised pilot and feasibility studies [46], including the numbers of prospective participants who were approached, deemed eligible and consented. The number of participants who received their intended treatment (including which elements of it) will be reported.

There are no formal stopping rules for this study as the primary aim is to assess feasibility. The primary focus will be on tabulated and graphical summaries of key indicators of success of the study, e.g. recruitment, engagement, retention and satisfaction with the Motiv8 intervention (participant and facilitator). Where applicable these will be reported with a 95% confidence interval. All adverse events will be reported. We will summarise the baseline demographic and clinical characteristics of each cohort by trial arm. The completion rate of assessments will be reported, as well as descriptive characteristics such as mean (SD), median (IQR) or number (percentage).

To determine the potential utility of the Motiv8 intervention, an appropriate regression model will be fit to the data, using our intended primary outcome (weight), with a trial arm as a covariate controlling for gender and ward type. *P*-values will not be reported as this study is not designed to test effectiveness—instead, 70, 80 and 90% confidence intervals for the difference in weight between Motiv8 and TAU. Alternative proposed primary outcomes such as cardiovascular fitness, physical activity and well-being will be explored.

As Motiv8 is delivered in cohorts, a degree of intra-cohort correlation will exist in the outcomes. A sample size calculation for a definitive trial will require an estimate of the intra-cohort correlation. The correlation in this study will be investigated, but the number of cohorts is likely to be too small to obtain an accurate estimate. We will use descriptive statistics to inform the design of the economic components of the definitive trial, based on completion rate and summaries of relevant data (ReQOL, EQ-5D, service use and engagement, treatments).

Qualitative interviews will be audio-recorded and transcribed verbatim. Thematic analysis will be conducted according to the five-phase procedure described by Braun and Clarke [47]: familiarisation; initial code generation; searching and identifying themes; reviewing themes; and defining and naming themes.

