### Limitations

*Small sample.* Due to resource and time constraints, the sample size for this pilot trial is small and consists of four cohorts of eight people (*n* = 32).*Mechanism of action.* It is unclear at this stage what the possible mechanisms of action may be for Motiv8 due to the multi-disciplinary approach.*Follow-up period.* Due to resource and time constraints, participants will only be followed up for 3 months after the end of the intervention, although proof of concept data will be collected at 6 and 9 months for the first two cohorts.*Lack of cultural diversity.* Only participants who have at least a basic understanding of English can take part as it will hinder their participation in the sessions and would not permit reliable estimates of the feasibility of outcome measures.*Waitlist control.* All participants will receive Motiv8 during the study which limits the scope of the follow-up assessments.

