### Participants

Participants will be current service users of low or medium-secure, adult forensic inpatient services in Greater Manchester Mental Health NHS Foundation Trust (GMMH NHS FT). The service provides individualised care and treatment for people with severe and enduring mental health disorders. We will aim to recruit a total of 32 participants forming four cohorts of Motiv8. Sample size is based on pragmatic limitations associated with the need to keep groups small due to the complex needs of service users, and the time constraints of funding. Following on from successful pilot work, clinical teams will be approached to identify eligible individuals to refer to the research team. The study will be advertised widely across the trust to service users and staff (such as through internal bulletins, social media, and recruitment materials). Clinicians will discuss the study with their service users and provide consent to contact. Researchers will provide potential participants with enough information to permit them to provide informed consent before taking part.

The inclusion and exclusion criteria are as follows:

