### Assessments

Assessments will be conducted at three timepoints; baseline (pre-intervention/waitlist), week after intervention/waitlist (10 weeks) and follow-up (12 weeks after the end of the intervention). Basic sociodemographic and clinical information will be collected at baseline (e.g. age, gender, ethnicity, diagnoses, physical health conditions, duration of illness, length of admission). Clinically relevant information will also be collected at all three timepoints (e.g. medication, service use, treatment plan), (See Fig. 2).

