### Progression criteria

A red/amber/green criterion for progression to a full trial will be used, with a stop/refine/go approach. This will likely be recruitment > 80% (green), 60–79% (amber), < 60% (red) of planned target; adherence > 70% (green), 50–69% (amber), < 50% (red) attendance at planned sessions; retention within the study > 75% (green), 60–74% (amber), < 60% (red) completion of proposed primary outcome for the definitive trial (weight). Retention to the proposed primary outcome measure for a definitive trial (change in weight) will be monitored.

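### The planned model for weight names gender and ward type but not baseline weight, so with four cohorts the Motiv8–TAU estimate is needlessly imprecise and dominated by chance baseline imbalance

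*Protocol article*

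**What the plan says.** The Analysis section leaves the type of model open: "an appropriate regression model will be fit to the data". It does state the outcome and the terms in that model: "using our intended primary outcome (weight), with a trial arm as a covariate controlling for gender and ward type". No p-values will be reported. The result will be given as "70, 80 and 90% confidence intervals for the difference in weight between Motiv8 and TAU". The same section says that a detailed statistical analysis plan will follow and that correlation within cohorts will be investigated.

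Weight is measured at baseline. The Assessments section says "Assessments will be conducted at three timepoints; baseline (pre-intervention/waitlist" and goes on to 10 weeks and a later follow-up; height and weight (for BMI) are listed among the physical measures. The waitlist arm receives Motiv8 after the 10-week assessment, so 10 weeks is the only time at which Motiv8 is compared with TAU alone.

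The Progression criteria name the endpoint in two ways in consecutive sentences: "completion of proposed primary outcome for the definitive trial (weight", and then "Retention to the proposed primary outcome measure for a definitive trial (change in weight) will be monitored".

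On size, Limitations says "the sample size for this pilot trial is small and consists of four cohorts of eight people", and Participants says "Sample size is based on pragmatic limitations associated with the need to keep groups small due to the complex needs of service users". Cohorts, not individuals, are randomised, by minimisation on factors that the article does not name.

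**The concern.** The article leaves the type of model open but states the outcome, the quantity to be reported and the controls. Baseline weight is not among the controls. Body weight normally changes little over 10 weeks compared with how much it varies between people, so a person's starting weight should explain most of the variance in the outcome. Gender and ward type cannot stand in for it.

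With four randomised units, mean weight at entry will almost certainly differ between arms by some kilograms. A comparison of follow-up weight carries that difference into the estimate nearly in full. What is at stake is the trial's indication of potential utility on its intended definitive primary outcome, and the variance information that a definitive sample-size calculation would draw on.

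**Working it through.** **The plan's own figure.** 4 cohorts × 8 people = 32, as stated. The size is pragmatic: no power, effect size, SD or intra-cohort correlation (ICC) is given, so there is nothing further to reproduce.

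**Assumptions (none from the article).** SD of weight 20 kg (range 15 to 25); ICC 0.05 (range 0 to 0.10), the same before and after adjustment; baseline to follow-up correlation r = 0.95 (range 0.90 to 0.98); two cohorts of eight per arm; normal multipliers; gender ignored.

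**Formulas.**
- Design effect: DE = 1 + (8 − 1) × ICC.
- SE, follow-up weight: SD × √(DE × 2/16).
- SE, adjusted for baseline: the above × √(1 − r²).
- SE, change score: the above × √(2(1 − r)).

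**Central case.**
- DE = 1 + 7 × 0.05 = 1.35.
- Follow-up weight: 20 × √(1.35 × 0.125) = 8.22 kg.
- Adjusted: 8.22 × √(1 − 0.9025) = 8.22 × 0.312 = 2.57 kg.
- Change score: 8.22 × √0.10 = 2.60 kg.

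| Interval | Multiplier | Half-width, follow-up weight | Half-width, baseline-adjusted |
|---|---|---|---|
| 70% | 1.036 | 8.5 kg | 2.7 kg |
| 80% | 1.282 | 10.5 kg | 3.3 kg |
| 90% | 1.645 | 13.5 kg | 4.2 kg |

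**Range.** Under these assumptions the proportional cut in SE depends on r alone. It is 1 − √(1 − 0.81) = 56% at r = 0.90, 69% at 0.95, and 1 − √(1 − 0.9604) = 80% at 0.98. Over all the assumed values the SE is 5.3 to 11.5 kg unadjusted and 1.1 to 5.0 kg adjusted.

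**Chance imbalance.** The baseline difference between arms has the same SE as the unadjusted estimate. The probability that it exceeds 3 kg in either direction is 72% in the central case and 57% to 79% over the range.

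**Simulation.** 20,000 trials with SD 20 kg, ICC 0.05 at baseline, r = 0.95 and an assumed true effect of −3 kg; arm and ward type in the model, gender omitted.

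| Outcome modelled | Mean estimate | SD of estimate | Wrong sign | Correlation with baseline difference |
|---|---|---|---|---|
| Follow-up weight | −2.96 kg | 8.15 kg | 36% | 0.96 |
| Change in weight | −3.00 kg | 2.25 kg | 9% | −0.18 |
| Follow-up weight adjusted for baseline | −3.00 kg | 2.26 kg | 9% | 0.00 |

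The means show no bias in any version; the spread and the last column show the problem. The simulated adjusted SD (2.26) is below the formula's 2.57 because the simulation adds no cohort-level variation after baseline.

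**Limits.**
- Cohort-level variation that arises after baseline, for example through shared delivery, adds the same amount to both variances. It therefore pulls their ratio towards 1 and shrinks the gain.
- Four cohorts with an intercept, arm and one cohort-level covariate leave 4 − 3 = 1 degree of freedom between cohorts. The 90% t multiplier is then 6.31 rather than 1.645, so the half-widths above are optimistic with or without adjustment.

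**The case against.** **The analysis plan will deal with it.** The article defers detail to a plan that is not shown, speaks only of an appropriate model, and never says that its covariate list is complete. This stands in part: the analysis plan may already include baseline weight, and the article does not rule it out. But the article chose to publish an outcome and controls, and an analysis that follows them leaves out the most useful one.

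**The endpoint is change in weight.** If change is what is modelled, the imprecision largely goes (SE 2.60 against 2.57 kg with adjustment). That is correct. However, the Progression criteria use both terms, in sentences about retention, and the Analysis section reports a difference in weight. The text does not say which is meant.

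**The size rests on assumptions.** It does. SD, r, ICC and the even split of cohorts are not in the article. Gender, already in the planned model, would absorb some of the variance in weight and reduce the gain somewhat.

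**Stronger readings that a reader might infer.** One is that the estimate shows entry weight instead of what Motiv8 did, or is confounded. The documents do not support this: allocation is randomised, the estimate still contains the treatment effect, and it is unbiased over randomisations. Another is that adjustment is worth about ten times the sample, from 1/(1 − 0.95²) = 10.3. That figure takes no account of variation between only four cohorts. A third is that this is the trial's only between-arm estimate. The article also says that fitness, physical activity and well-being will be explored.

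**Conclusion.** The point holds as one of precision and of clarity about the endpoint. Modelled as written, follow-up weight gives an unbiased but very imprecise estimate which, in the one trial that will be run, mostly tracks the baseline difference between two pairs of cohorts. At an assumed SD of 20 kg and r of 0.90 to 0.98, adjustment cuts the SE by roughly 56% to 80%, and by less if cohorts diverge after baseline. It does not cure the shortage of clusters, so the absolute half-widths should not be taken as what this trial will achieve.

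Severity is moderate. The primary aim is feasibility, no p-values are planned, and progression turns on recruitment, adherence and retention.

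**What to change.** - Add each participant's baseline weight as a covariate in the model of 10-week weight. Keep trial arm, gender, ward type and whatever allowance is made for cohort.
- Use one definition in the Analysis section and the Progression criteria: the baseline-adjusted difference in weight at 10 weeks. With baseline weight in a linear model, taking 10-week weight or change as the outcome gives the same arm coefficient, so this wording reconciles the two terms.
- Adjust the alternative outcomes (fitness, physical activity, well-being) for their own baseline values.
- Report the baseline to 10-week correlation for the definitive sample-size calculation.

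The cost is a few lines in the analysis plan and no new data. One caution: baseline weight should enter at the level of the individual. In an analysis of four cohort means, an intercept, arm, ward type and mean baseline weight would leave 4 − 4 = 0 degrees of freedom.

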## Methods and analysis

### Trial design and flow chart

All procedures and conduct of this trial will be conducted in line with the CONSORT Extension to Randomised Controlled Trials [31]. The design is a prospective, single-blind, cluster-randomised controlled feasibility trial with two conditions; weight management intervention (Motiv8) plus treatment as usual (TAU), versus TAU waitlist control (with Motiv8 delivered after TAU). The study will take place in adult secure, forensic NHS mental health services. TAU will be measured throughout, and no treatment will be withheld from participants. Assessments will be completed at baseline (pre-intervention), 10 weeks (the week after participants finished Motiv8 or TAU), and again 12 weeks after the end of the intervention period (12-week follow-up). A nested qualitative study will explore the subjective experiences of taking part in Motiv8 and the acceptability of the intervention. See Fig. 1 for a summary of the trial design. The trial is prospectively registered on the ISRCTN registry: ISRCTN13539285 (ISRCTN-ISRCTN13539285: Motiv8: A weight management intervention for adults in secure mental health inpatient services). An independent Trial Steering Committee (TSC) and Experts by Experience Group have been established to provide ongoing guidance and oversight of the study.

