### Randomisation and blinding

Individuals will be cluster randomised by cohort, using minimisation to ensure balanced distribution. Following written consent, cohorts will be randomised using a free web-based system (www.sealedenvelope.com). Allocation will be communicated to the CI, study management team and facilitators but not research assistants, statistician or health economist. Participants will be informed of their randomisation status by letter or via clinicians, communicated via the administrator.

Blinding of allocation will be maintained for research assistants until all outcome measures for all subjects have been collected. Blindness will be maintained using a range of measures (e.g. separate offices for facilitators and researchers, protocols for answering phones, secretarial support). Unblinding will be communicated to the CI, and if possible, future assessments will be conducted by a blinded assessor. This may not always be possible due to the trial being cluster randomised, and therefore unblinding will occur on a cohort basis. Maintaining rater blindness to treatment allocation is crucial, and the TSC will be consulted in the instance that any unblinding occurs and implement corrective action if necessary.

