### Trial status

The trial begun recruitment in December 2021. Recruitment will occur in two stages (to allow recruitment of the four clusters on a ward-by-ward basis) and will be complete by approximately July 2022 for the main cohort. The staff sub-study begun recruitment in December 2021. The study has been granted an extension to September 2023. Final outcome data will be collected by August 2023 and analysis completed by September 2023. A trial paper with outcomes is expected to be submitted for publication by January 2024.

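### The weight model as listed has no cohort term, so its 70/80/90% intervals would be too narrow for any positive intra-cohort correlation unless cohort is allowed for

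*Protocol article*

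**What the plan says.** The unit of randomisation is clear. Under Randomisation and blinding: "Individuals will be cluster randomised by cohort, using minimisation to ensure balanced distribution". Under Participants: "We will aim to recruit a total of 32 participants forming four cohorts of Motiv8". The Limitations section gives the cohort size ("consists of four cohorts of eight people"), and Trial status again counts four clusters ("to allow recruitment of the four clusters on a ward-by-ward basis"). Trial design names two arms ("cluster-randomised controlled feasibility trial with two conditions"). The number of cohorts per arm is not given; two per arm follows from balanced allocation of four.

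Under Analysis, the potential utility of Motiv8 is to be judged from a weight model: "an appropriate regression model will be fit to the data, using our intended primary outcome (weight"). Its listed terms are trial arm, gender and ward type. No p-values are planned; the model yields "70, 80 and 90% confidence intervals for the difference in weight between Motiv8 and TAU".

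The next paragraph of the same section begins: "As Motiv8 is delivered in cohorts, a degree of intra-cohort correlation will exist in the outcomes". It then links this correlation to the sample size of a definitive trial and warns that the cohorts are too few to estimate it well. It does not link the correlation to the intervals.

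**The concern.** The effect of arm is estimated from the differences between randomised cohorts. With four cohorts in two arms, 4 − 2 = 2 df are available to estimate the error of that comparison. A participant-level fit of the listed terms to 32 people claims 32 − 4 = 28 df and treats people in one cohort as independent. It therefore understates the standard error and also uses too small a multiplier.

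The interval levels matter because they replace p-values as the only stated measure of uncertainty about the weight effect. A reader who sees a 90% interval will take the level at face value. Ward type adds a further difficulty: the Exclusion section says each cohort should come from one ward where possible, so ward type is largely a characteristic of the cohort. Adjusting for it uses one of the two df.

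**Working it through.** **Inputs from the article.** Four cohorts of 8; cohort as the randomised unit; two arms; model terms arm, gender and ward type; levels 70, 80 and 90%. The planned total reproduces: 4 × 8 = 32. There is no power calculation to reproduce.

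**Assumptions.** Two cohorts per arm. ICC of 0.01 to 0.20, since none is given. In the simulation of the full listed model, each arm has one cohort of each ward type and each cohort is half one gender. The outcome SD cancels out of coverage and of width ratios.

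**Step 1, variance.** Design effect = 1 + (8 − 1) × ICC, which is 1.07 at ICC 0.01, 1.35 at 0.05, 1.70 at 0.10 and 2.40 at 0.20.

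**Step 2, multipliers.** Two-sided t quantiles:

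| Level | 28 df | 2 df | 1 df |
|---|---|---|---|
| 70% | 1.056 | 1.386 | 1.963 |
| 80% | 1.313 | 1.886 | 3.078 |
| 90% | 1.701 | 2.920 | 6.314 |

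**Step 3, coverage.** 100,000 simulated trials per ICC, ordinary least squares on participants with no allowance for cohort. Cells give actual coverage (%) of the nominal 70/80/90% intervals.

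| ICC | Arm, ward type, gender | Arm only | Cohort means, t on 2 df |
|---|---|---|---|
| 0 | 69.9/79.8/89.8 | 69.8/79.8/89.8 | 69.9/79.9/90.0 |
| 0.01 | 68.3/78.4/88.8 | 68.3/78.5/88.8 | 70.0/80.0/90.0 |
| 0.05 | 62.0/72.3/83.8 | 62.3/72.6/84.0 | 70.1/80.0/90.0 |
| 0.10 | 55.8/66.0/78.1 | 56.4/66.6/78.6 | 70.0/80.1/90.1 |
| 0.20 | 46.5/55.9/68.1 | 47.6/57.1/69.2 | 70.0/80.1/90.0 |

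The shortfall is 1 to 2 points at ICC 0.01, about 6 to 8 at 0.05 and about 12 to 14 at 0.10. With 6 people analysed per cohort (75% retention), the listed model covers 64.0/74.2/85.4% at ICC 0.05, so the pattern does not depend on complete follow-up.

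**Step 4, does a random effect alone repair this?** Not with normal quantiles. With four cohorts, REML sets the between-cohort variance to zero in about 50% of simulated trials at ICC 0.05 and about 41% at 0.10. The nominal 90% interval then covers 87.8%, 85.0% and 81.6% at ICC 0.05, 0.10 and 0.20. This is better than ignoring cohort, but still short.

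**Step 5, cost in width at the 90% level.** The ratio of a cohort-level to a participant-level interval is (2.920 / 1.701) × √(design effect):

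- ICC 0.05: 1.717 × √1.35 = 1.717 × 1.162 = 1.99
- ICC 0.10: 1.717 × √1.70 = 1.717 × 1.304 = 2.24

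If ward type is kept as a cohort-level covariate, 1 df remains, and the ratio at ICC 0.05 is (6.314 / 1.701) × 1.162 = 4.31.

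**The case against.** The strongest reply is that the article does not fix a participant-level model. It says only that the regression will be appropriate. A random effect, robust errors or a cluster-level analysis need not appear in a list of covariates. A separate analysis plan is promised, and reporting is to follow the CONSORT guidance for cluster randomised pilot and feasibility studies. This stands. A reader might infer that the intervals are bound to be too narrow; the article does not support that, and the point has to be conditional on fitting the terms as listed. The reply does not remove the point. The article itself fixes the covariates and levels, states that the correlation will exist, and gives it only one use, which is another trial's sample size. A reporting guideline does not change the model.

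A second reply is that the ICC is unknown and may be small. That also stands: at 0.01 the loss is slight. But the article gives no ground for assuming a value so low.

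Two stronger readings are tempting and unsupported. One is that a decision to proceed would rest on an overconfident effect estimate. The Progression criteria use recruitment, attendance and retention only, and the Analysis section says the study is not designed to test effectiveness. The other is that the 95% intervals for the feasibility indicators share the fault. The article promises these only where they apply and names no method, so nothing stated can be faulted.

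**Conclusion.** The point holds in conditional form. Four cohorts are randomised, the listed model has no cohort term, and the acknowledged correlation is not connected to the intervals. If the model is fitted as listed with independent errors, coverage falls below the stated level for every positive ICC: slightly at 0.01 and materially from about 0.05, where the 90% interval covers about 84%. The sizes rest on assumed ICCs, on an inferred two cohorts per arm, and on cohorts of 8.

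Severity is moderate. The interval is the article's only measure of uncertainty for the weight effect, but it decides no progression criterion and no hypothesis test depends on it.

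**What to change.** State in the analysis plan that the 70/80/90% intervals are computed at the level of randomisation, by one of two routes:

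- adjust each person's 10-week weight for baseline weight, average within cohort, compare the cohort means between arms, and use t on 2 df; or
- fit a cohort random effect with a named small-sample df correction, not normal quantiles.

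Drop ward type from the interval model, or say that it leaves about 1 df (90% multiplier 6.314 against 2.920). If gender also turned out to vary only between cohorts, no df would remain, so the plan should say what happens then. Show the four cohort results beside the interval and label the interval as descriptive.

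The work is a few lines of plan text and a simple analysis. The real cost is precision: 90% intervals about 2.0 to 2.2 times as wide for ICC 0.05 to 0.10. That width is what four randomised cohorts can support.
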